*Sample size:* We based our sample size requirements on the primary outcome for discharge reconciliation—difference in the rate of adverse drug events—as this binary outcome with correlated patient observations required the maximum sample size (appendix 1). For this outcome, we bracketed expected rates of adverse drug events in the control group based on recent Canadian and American studies to be between 10% and 19%. We specified an absolute reduction of 5% as being the smallest clinically relevant difference that would be worthwhile to detect. A difference of this magnitude would conservatively result in 96,000 fewer adverse drug events in Canada annually, at an overall estimated annual cost-savings of \$240million. Specifying an acceptable Type 1 error of 5%, and Type 2 error of 20%, the estimated sample size for the expected range in possible cluster correlations ( $r=0.02-0.05$ ) varies from 2,852 to 4,423 patient admissions, assuming a baseline rate in the control group of 15%, midway between 10% and 19%. Based on an analysis of re-admission rates in 2008, a cluster correlation no greater than 0.03 is expected, which would mean a sample size of 3,376 is required to detect a 5% reduction in adverse drug events. Based on our prior work, we estimate that 10% of patients will not be reached to complete the post-discharge follow-up interview, therefore we estimate that we will need to recruit 3,714 patients to achieve our sample size requirements. Overall, in 2008, there were 17,480 admissions to the MUHC, of which 12,236 were admitted to eligible medical, surgical and psychiatric units. Based on our pilot study, approximately 42% ( $n=5,139$ ) of patients will be eligible for inclusion (i.e. have public drug insurance,  $\geq 18$  years old, first admission in study period, alive at discharge), and of these 3% will refuse to participate, 45% will not be asked for consent because the staff are too busy, and 52% will consent to participate. By providing staff with support to obtain consent from patients, we expect that we can increase the proportion of eligible patients participating to 60%, or 257 per month. Assuming 10 months per year of active recruitment to account for summer and winter holidays, we estimate that it will take 15 months, or approximately 1.5 years to recruit all patients. With an average length of stay of 8.9 days, we can successfully complete enrollment and follow-up in 18-20 months.

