*Randomization:* The 28 hospital units will be assigned a random number, stratified by type (medicine, surgery, psychiatry), and the default random number generator in SAS will be used to randomly assign units within stratum to electronically enabled discharge reconciliation or usual care. There will be approximately 1,857 patients who are assigned to medication reconciliation at discharge, 1,857 to usual care.

---

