**Bias Control** The main challenge in *bias control* is the inability to blind staff to treatment assignment, and potential co-intervention. To control bias, the research assistant, expert panel, and analyst assessing the outcome of treatment will be blinded to unit and treatment allocation status. To assess bias related to possible co-interventions, the project coordinator will conduct a monthly review with the unit directors and hospital pharmacy to assess co-interventions (new initiatives that may modify the study outcomes), and we will use sensitivity analysis to assess the potential impact on the study outcomes. As the involvement of the hospital pharmacist in the patient's care likely reduces the risk of adverse events (e.g. through medication review), we will retrieve this information from the chart and assess whether hospital pharmacist intervention (yes vs. no) is a confounder by including this information as a patient-level variable in the analysis. In addition, as cluster randomization may not produce patients groups who have an equivalent risk of adverse events post-discharge (i.e. because randomization is by unit rather than by patient), we will assess whether patients admitted to the usual care vs. e-discharge units had a similar rate of hospitalizations, and ER visits in the 12 months prior to admission using RAMQ medical service data retrieved for each patient, and include prior ER/hospitalization history in the analysis to determine if it confounds the estimated effect of the intervention.

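### Patients are recruited after units are randomized, by staff who cannot be blinded, and no visible rule keeps the choice of whom to approach independent of arm

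*Protocol*

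**What the plan says.** Allocation comes first. Under Study Population, Randomization, the 28 units are numbered and SAS is used to "randomly assign units within stratum to electronically enabled discharge reconciliation or usual care".

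Recruitment of individual patients follows, over about 15 months. Of eligible patients, the Sample size paragraph expects from the pilot that "of these 3% will refuse to participate", that "45% will not be asked for consent because the staff are too busy", and that "52% will consent to participate". It then continues: "By providing staff with support to obtain consent from patients", participation should rise to 60%. Under Eligibility, a patient who cannot consent enters on the authority of the family, if present, or of the admitting unit's medical director.

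The Bias Control paragraph names as its main difficulty the "inability to blind staff to treatment assignment, and potential co-intervention". Blinding is reserved for the interviewer, the expert panel and the analyst. The paragraph accepts that the arms may differ in risk, but puts this down to randomizing units rather than patients. Its response is to compare prior-year hospital and ER use and to "include prior ER/hospitalization history in the analysis to determine if it confounds the estimated effect of the intervention".

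Data Management and Analysis describes the arms by age, sex, prior visits and hospitalizations, medications and Charlson index, and follows CONSORT in documenting the eligibility and follow-up of patients and units. The primary model is a logistic GEE with a dummy variable for the intervention. Whether adjustment for co-interventions or baseline differences changes the effect is to be assessed afterwards.

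**The concern.** Randomizing units makes the patients admitted to the two arms comparable in expectation. The analysis uses the patients recruited, which is a smaller group. If people who know the allocation decide whom to ask, comparability rests on their asking in the same way in both arms, and randomization does not secure that.

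There is a plausible route to a difference. On intervention units the physician reconciles every drug and records a reason for each stop or dose change, so a patient on many drugs may mean more work there, and workload is the stated reason for not asking.

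A difference in recruitment biases the primary comparison, and a larger sample does not shrink it. The planned response is weak in two ways. Whether the adjusted estimate is used depends on what the data show, with no criterion given. And adjustment reaches only the measured part of risk among patients who were enrolled. The loss-related bias check concerns patients lost after discharge, and post-discharge claims are described for consenting patients, so patients never asked would have no outcome to compare.

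**Working it through.** **Step 1. Reproduce the recruitment figures (Study Population, Sample size).**
- Eligible per year: 12,236 × 0.42 = 5,139, as stated.
- Pilot split: 3% + 45% + 52% = 100%.
- Monthly recruitment: 5,139 × 0.60 / 12 = 257, as stated.
- Duration: 3,714 / 257 = 14.5 months, stated as 15.

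**Step 2. Share not asked.**
- Pilot split: 45% of eligible patients, or 45/48 = 94% of all non-participation.
- At 60% participation with refusals still 3% of eligible patients: 100 − 60 − 3 = 37%, or 37/40 = 93% of non-participation.
- If refusal scales with asking instead: 52/55 = 94.5% of those asked consent, so 60/0.945 = 63.5% must be asked and 36.5% are not.

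Either way, who takes part is decided almost wholly by who is approached.

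**Step 3. Illustration with no true effect; the risk ratios are assumed.** The documents do not give the risk of non-enrolled patients relative to enrolled ones; call it R. Suppose one arm enrols a representative sample at the protocol's 15% control rate and the other enrols a fraction f of its eligible patients. From 0.15 = f·r + (1 − f)·R·r, the enrolled risk is r = 0.15 / [f + (1 − f)R].

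| R (assumed) | r at f = 0.60 | 15% − r, points | 15% − r at f = 0.52, points |
|---|---|---|---|
| 0.5 | 0.15/0.80 = 18.75% | −3.75 | −4.74 |
| 0.8 | 0.15/0.92 = 16.30% | −1.30 | −1.59 |
| 1.1 | 0.15/1.04 = 14.42% | 0.58 | 0.69 |
| 1.25 | 0.15/1.10 = 13.64% | 1.36 | 1.61 |
| 1.5 | 0.15/1.20 = 12.50% | 2.50 | 2.90 |
| 2 | 0.15/1.40 = 10.71% | 4.29 | 4.86 |

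If the selecting arm is the intervention, a positive entry is a false benefit and a negative one a false harm; if it is usual care, the signs reverse. If both arms select in the same way, the difference is zero.

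**Step 4. A milder illustration, also assumed.** One third of eligible patients have 25% risk and two thirds 10%, so the mean is 15%. Both arms enrol 60% overall, but high-risk uptake in one arm is 45% or 50% instead of 60%.
- At 45%: high-risk share (1/3 × 0.45)/0.60 = 0.25; rate 0.25 × 25% + 0.75 × 10% = 13.75%; difference 1.25 points. Low-risk uptake must then be (0.60 − 0.15)/(2/3) = 67.5%.
- At 50%: share 0.278; rate 14.17%; difference 0.83 points; low-risk uptake 65%.

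That is 17% to 25% of the 5-point target.

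**The case against.** The protocol gives workload as the reason for not asking, not patient risk. It says only staff, without saying that they belong to the randomized units. Consent is described around admission, and most patients come through the emergency department, so some of those asking may serve both arms. The intervention's launch support lasts two weeks per unit and concerns the discharge prescription, not consent; the consent support is nowhere described as differing by arm. Baseline comparison, CONSORT reporting and blinded outcome assessment are all planned. Some text is absent from the public copy, and a consent procedure may stand there. The exact covariate list is normally left to the SAP.

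Much of this stands. A reader might infer that unit staff pick lower-risk patients, or that the launch and champions push enrolment in a known direction. The documents support neither: risk-related asking is an inference, and more engaged staff could as easily enrol more complex patients.

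What remains is that the visible text does not say who approaches patients or in what order, while the largest loss between eligibility and enrolment occurs at exactly that step. At least one entry route, for patients unable to consent, can depend on the head of a randomized unit. The baseline tables and CONSORT counts would reveal an imbalance, not prevent it. As for the SAP, the objection here is to a rule the protocol itself states, test and then perhaps adjust, not to a missing list.

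**Conclusion.** The point holds as a gap in safeguards, not as a demonstrated bias. Recruitment follows allocation, staff who cannot be blinded carry it out, and 45% of eligible patients on the pilot figures, or about 37% under the plan, are not asked. The arms may therefore differ in risk through recruitment, and the visible text contains no rule against it.

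The direction and size are unknown. The 0.8 to 1.3 points of the milder illustration and the 0.6 to 4.3 points at 60% participation with R from 1.1 to 2 rest wholly on assumed inputs and are before any adjustment; the second set also requires selection in one arm only. They show that a modest difference in asking could matter against a 5-point target, not that it will occur. If consent text outside the public copy already fixes the order of approach, the first part of the fix reduces to a cross-reference.

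**What to change.** In Study Population, Sample size, state that the planned consent support is given identically in both arms, and that eligible patients are approached consecutively from the admission list as capacity allows. When staff run out of time, list order then decides who is missed, not a judgement made with knowledge of the arm. Report eligible, approached and consented counts per unit and per arm within the CONSORT documentation already planned.

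In Bias Control and in Data Management and Analysis, replace the test of confounding with a primary GEE model that always adjusts for age, sex, Charlson index and prior-year ER visits and hospitalizations.

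The cost is slightly more screening record-keeping and a few sentences of protocol text; the covariates are already to be collected. The adjusted odds ratio is conditional on those covariates and should be labelled so. Separate recruiters and screening of RAMQ claims before consent are not needed: the first would need extra staff, and the second might need privacy clearance.

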## Study Design

A randomized cluster design will be used to determine if electronically-enabled discharge reconciliation reduces adverse events post discharge. The study population will be patients admitted to medical, surgical, and psychiatric units at the McGill University Health Center. Patients will be stratified by medical, surgical or psychiatric admission, and a cluster randomization approach will be used to allocate the 16 medical, 10 surgical, and 2 psychiatric units to discharge reconciliation and communication versus usual care (Figure 3).

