## Study Population

**Eligibility:** The target population comprises patients who are at risk of preventable adverse drug events during transitions between community and hospital care. This population represents approximately 60% of the 3.1 million patients admitted to hospital each year in Canada, of whom 93,000 to 428,000 are expected to experience an adverse drug event. The study will be conducted at the McGill University Health Centre, a network of teaching hospitals that serve a population of 1.3 million Quebecers from Montreal to James Bay, including a trauma center, two tertiary adult hospitals, a psychiatric facility and a specialized hospital for respiratory disease. Teaching hospitals represent approximately 28% of hospital beds in

Canada, but they treat a higher proportion of complex, vulnerable patients where improvements in medication safety would have the greatest benefit. Patients will be eligible for inclusion in the study population if they are: 1) using prescription medication at admission, 2) covered by the Quebec drug insurance plan, 3) admitted from the community, 4)  $\geq 18$  years old at admission, 5) admitted to a general or intensive care medical, surgical or psychiatric unit, 6) discharged alive. Patients who are cognitively impaired or otherwise unable to provide consent will be included as we have shown that this subpopulation of patients may be at greatest risk of adverse events because of communication problems. Tri-council ethics guidelines deem that this subpopulation should not be excluded from interventions that potentially provide direct benefit to the participant because of the inability to provide informed consent (Article 4.5). For these patients, the family if present, or the medical director of the admitting unit will authorize study participation. Demographic, clinical and health care service use characteristics of the study population will be retrieved from the admission note, and provincial health care administrative databases in the year before admission and in the two months after discharge to characterize the study population, evaluate the integrity of randomization, assess potential biases related to losses to follow-up, and assess re-admission.

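### The 28 units are randomised within unit type only. Hospital site, unit volume and 2008 unit data are left out of the allocation, so chance imbalance that could be cheaply avoided remains.

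*Protocol*

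**What the plan says.** The Study Design section plans to "allocate the 16 medical, 10 surgical, and 2 psychiatric units to discharge reconciliation and communication versus usual care". The Randomization paragraph under Study Population gives the method: "The 28 hospital units will be assigned a random number, stratified by type (medicine, surgery, psychiatry"), after which "the default random number generator in SAS will be used to randomly assign units within stratum". Type is the only restriction named. An equal split within each type is not stated, though the paragraph expects about 1,857 patients per arm.

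The Eligibility paragraph describes the centre as a network of teaching hospitals, "including a trauma center, two tertiary adult hospitals, a psychiatric facility and a specialized hospital for respiratory disease". It does not say how many study units each facility supplies.

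The Sample size paragraph shows what was available before allocation. For volume, it reports that in 2008 "12,236 were admitted to eligible medical, surgical and psychiatric units". For outcome variation it says: "Based on an analysis of re-admission rates in 2008, a cluster correlation no greater than 0.03 is expected".

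The Bias Control paragraph recognises that "cluster randomization may not produce patients groups who have an equivalent risk of adverse events post-discharge". Its response is to compare prior-year hospitalisations and emergency visits between arms and to include that history in the analysis. Data Management and Analysis specifies a logistic GEE clustered on unit. Adjustment for co-interventions and baseline differences is to be assessed, and unit type enters only as an effect modifier in secondary analysis. Site and unit volume are not named.

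**The concern.** With 28 clusters, chance differences between units matter far more than they would with patient-level randomisation. Type explains some of those differences. Hospital, with its case mix, discharge practice and local initiatives, may explain more, and so may volume and past re-admission rate.

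A cluster correlation cannot be estimated from re-admission rates without data by unit, so the sponsor very probably holds a 2008 rate for each unit. That information was used to size the trial and not to balance it.

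The stakes are balance and precision. If one hospital's units lean to one arm, site-level co-interventions of the kind Bias Control plans to monitor become partly entangled with treatment. A patient's own prior use of hospitals does not capture them.

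**Working it through.** **Inputs from the protocol.** 16 medical, 10 surgical and 2 psychiatric units (Study Design). Control rate 15%, target reduction 5 points, cluster correlation 0.02 to 0.05 with 0.03 expected, and 3,714 patients to recruit (Sample size).

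**Assumed, because not stated.** Splits of 8:8, 5:5 and 1:1 within type; the spread of units over sites; the variation in unit size.

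**1. The plan's own arm size.** 3,714 / 2 = 1,857, which reproduces. It is the expected size under equal allocation and is stated as approximate.

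**2. Chance difference between arms.** For a binary outcome with rate p and cluster correlation r, the between-unit SD is √(r·p·(1−p)). At r = 0.03 this is √(0.03 × 0.15 × 0.85) = 0.0618, or 6.2 points. For the difference between two means of 14 equally weighted units, the SD is 6.2 × √(2/14) = 2.3 points.

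| r | Between-unit SD (points) | SD of arm difference (points) |
|---|---|---|
| 0.02 | 5.0 | 1.9 |
| 0.03 | 6.2 | 2.3 |
| 0.05 | 8.0 | 3.0 |

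At 0.03 this is nearly half of the 5-point target (2.3 / 5 = 0.47). It needs no assumption about sites. It counts all between-unit variation, so whatever part type explains is already removed by the existing strata.

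**3. Site imbalance (illustrative).** If a site has k of the 16 medical units and the stratum splits 8:8, the chance that all k fall in one arm is 2·C(16−k, 8)/C(16, 8), with C(16, 8) = 12,870.

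| k | All in one arm |
|---|---|
| 2 | 7/15 = 47% |
| 3 | 20% |
| 4 | 7.7% |
| 5 | 2.6% |

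Small sites are the ones at risk. For a large site, suppose two hospitals each have 8 medical and 5 surgical units. Combining the two hypergeometric distributions, a hospital has 9 or more of its 13 units in one arm with probability 12%, and 10 or more with probability 2.0%. All 8 medical units in one arm has probability 2/12,870, about 0.016%.

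**4. Volume imbalance (illustrative).** Simulating 28 unit sizes under the same splits, the chance of an arm split worse than 55:45 is about 18%, 37% and 49% at assumed coefficients of variation of 0.4, 0.6 and 0.8. Unit volumes are not printed, so none of these can be picked as the actual figure.

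**5. Room for a constraint.** There are 12,870 × 252 × 2 = 6,486,480 allocations with 8/8, 5/5 and 1/1 splits, so many would remain after a moderate balance criterion.

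**The case against.** The best defence is that stratified cluster randomisation is a sound and common design and that nothing in the protocol is contradictory. Type is balanced. Prior use of hospitals is compared and included in the analysis. Age, sex, visits, hospitalisations, medications and co-morbidity are checked, and adjustment for baseline differences is assessed for both outcomes. Model terms may also be settled in an analysis plan that is not at hand. All of this stands, and it is why the point is an improvement and not a defect. It does not remove the point, because the allocation method is fixed in the protocol and cannot be repaired after the draw, and the named covariates are patient-level.

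A reader might infer several stronger things that the documents do not support:

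- **That the 28 units come from five different hospitals.** The protocol describes the network as including those facilities. It does not say which supply units or how many, and the design figure is missing from the text available.
- **That a main hospital is likely to be confounded with arm.** Under the two-hospital layout above, 10 or more of 13 units in one arm occurs only 2.0% of the time. One can instead count the chance of 6:2 or worse in medicine (13%) or 4:1 or worse in surgery (21%). That gives 1 − 0.868 × 0.794 = 31%, but it includes cases where the other stratum offsets the imbalance.
- **That power would rise by a known amount.** With 3,376 patients in 28 units at r = 0.03, power for 15% versus 10% is about 54%. It would be 63% or 75% if the factors explained 25% or 50% of between-unit variance. The documents support neither share; t quantiles on 20 degrees of freedom lower these two figures to about 58% and 71%; and the gain comes from adjustment as much as from constraint. The 2008 rates are re-admissions, and nothing shows how well they track adverse drug events by unit.
- **That 1,857 per arm is wrong.** It is given as approximate, and no printed unit size contradicts it.

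One could also ask whether placing both arms in each hospital raises contamination. The Study Design section locates contamination within units, and allocation by type already allows both arms in one hospital, so the constraint introduces no new kind of exposure. The sponsor should still confirm this.

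**Conclusion.** The point holds as a worthwhile, low-cost improvement to a valid design. Allocation uses unit type alone, while site, volume and (by sound inference) 2008 unit re-admission rates were available.

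The firm figure is an SD of about 2.3 points in the chance difference between arms at 15% and r = 0.03, with a range of 1.9 to 3.0 over the protocol's range of r. It assumes 14 equally weighted units per arm and takes no credit for the type strata. Balancing on further factors would remove part of it, but how much is unknown.

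The site and volume probabilities depend on assumed layouts and show only that imbalance is plausible, mainly for sites with few units. If both psychiatric units are in one facility, a 1:1 split already divides that site, and the concern is then confined to medicine and surgery.

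**What to change.** Before allocation, amend the Randomization paragraph as follows:

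1. State the splits: 8/8 medical, 5/5 surgical, 1/1 psychiatric.
2. Use covariate-constrained randomisation. List the 6,486,480 allocations. Keep those in which every site with two or more units of a type has that type in both arms, and in which the arms are close, within limits set in advance, on 2008 eligible admissions and 2008 unit re-admission rate.
3. Draw one retained allocation at random with a recorded seed, and report how many were retained.
4. In Data Management and Analysis, include unit type and the balancing factors in the primary GEE model.

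Crossing three types with site as further strata would be too thin for 28 units, which is why a constraint is preferable.

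The cost is a short program and about a paragraph of text. The downsides are a few degrees of freedom in the model and the need to keep the limits loose enough that many allocations remain. If allocation has already taken place, only the fourth step is open.
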